### Intervention

2.5

#### Arms and intervention

2.5.1

An authorization to conduct the CANSEP trial using THC and CBD manufactured by PurCann Pharma was obtained from Health Canada prior to the start of recruitment.

Participants will be allocated to four arms and initially receive THC (4 mg/day), CBD (40 mg/day), THC/CBD combination (THC 4 mg/day and CBD 40 mg/day), or placebo, on the first day. Every two days, the daily quantity will be multiplied by two up to a maximum of 20 mg for THC and 200 mg for CBD, if well tolerated (Table 1). The selection of doses is based on previous studies on cannabinoids in MS (19, 25–34), and on a systematic review indicating that a daily dose of 200 mg of CBD is effective for other neurological conditions and symptoms while being well tolerated (35). One of the authors’ expert opinion on cannabinoids in psychiatric research and clinical practice (36, 37), and the approved and available orally formulated cannabinoids in Canada (38, 39) also accounted for these doses’ selection. THC and CBD will be taken as softgels (cannabis extract; placebo will taste and look exactly the same), in two divided doses per day at 12-h intervals. Participants will receive the allocated treatment for a total of 4 consecutive weeks, followed by an additional 12 weeks of treatment for responders who will be identified as those who have a decrease from baseline in spasticity of at least one point on the mNRS. Participants enrolled in the trial will continue stable doses of other standard treatments for spasticity including muscle relaxants (baclofen, tizanidine, and clonazepam) (18).

**Table 1 tab1:** Medication dosage.

Treatment period (4 weeks)					
Week	Day	Daily THC dose (mg)^a^	Daily CBD dose (mg)^a^	Daily THC and CBD combined dose (mg)^a^	
				THC	CBD
W1	#1	4	40	4	40
	#2	4	40	4	40
	#3	8	80	8	80
	#4	8	80	8	80
	#5	16	160	16	160
	#6	16	160	16	160
	#7	20	200	20	200
W2 to W4 included		20	200	20	200
Extension period (12 weeks)					
Week		Daily THC dose (mg)^a^	Daily CBD dose (mg)^a^	Daily THC and CBD combined dose (mg)^a^	
				THC	CBD
W5 to W16 included		20	200	20	200

^a^Treatment will be taken in two divided doses per day at 12-h intervals. CBD, cannabidiol; THC, tetrahydrocannabinol; W, week.

#### Medical management

2.5.2

Regardless of the assigned arm, participants will receive medical examination and management from the study physician according to usual standards of care. Medication adherence will be monitored using a daily diary. The study pharmacist will count the unused capsules at the end of the 4 initial weeks of treatment and during the additional period of 12 weeks and will check for accuracy by comparing with the numbers mentioned on the daily diary reported by the participants.

### Assessments

2.6

#### Screening

2.6.1

At the screening visit, participants will be asked to provide sociodemographic information, their medication use, and their comorbidities. Furthermore, compulsive use and the individual’s preoccupation with cannabis use will be assessed by the Severity Dependence Scale, a self-reported questionnaire (40). The Structured Clinical Interview for DSM-5 Disorders will be administered to assess substance use disorders, including alcohol and other substances (41). The heart condition will be reviewed by electrocardiography. A pregnancy test and birth control questionnaire will be conducted in women aged ≤50 years with no sign of menopause and who did not undergo surgical contraception. A MS neurologist will evaluate the participants’ eligibility and will assess spasticity and disability with the Modified Ashworth Scale and the Expanded Disability Status Scale, respectively (42, 43).

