### Study population

2.3

The CANSEP study seeks to identify a cohort of PwMS according to the 2017 revised McDonald criteria (23), from the Centre hospitalier de l’Université de Montréal (CHUM) MS Clinic. Our study sample will be representative of the sex distribution of MS, which is 2.6 higher in women than in men in Canada (1). It will recruit adults of at least 21 years of age [the legal age in the province of Quebec to use cannabis products (24)], who reported a mean level of spasticity over 7 days of 2 points or more on the mNRS. All potential participants will be screened to determine their eligibility according to the following inclusion and exclusion criteria:

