Inclusion criteria: (a) Be diagnosed with MS (any subtype), for at least six months, by a MS neurologist, according to the 2017 revised McDonald criteria (23); (b) Spasticity or symptoms related to spasticity due to MS of at least one-month duration and not relieved with current therapy, at a mean level of 2 or more on the mNRS; (c) Have a stable dose of standard therapies for at least 4 weeks prior to the screening visit and willingness to maintain such therapies for the duration of the study; (d) Aged 21 years or older (24); (e) Have the ability, in the investigator’s opinion, and willingness to comply with all study requirements; (f) Able to speak and read French or English (grade nine level of language required).Exclusion criteria: (a) Concomitant disease with symptoms of spasticity, or that may have influenced their level of spasticity; (b) Received a botulinum toxin injection within four months prior to the screening visit or unwillingness to stop receiving botulinum toxin injections for the duration of the study; (c) Use of cannabis or cannabinoid-based products within 7 days prior to study entry and unwillingness to abstain from use of cannabinoids for the duration of the study; (d) History of schizophrenia, other psychotic illness, or other significant psychiatric disorder other than anxiety or depression associated with their underlying condition; (e) Alcohol or substance abuse disorder other than nicotine; (f) History of epilepsy or recurrent seizures; (g) Hypersensitivity to cannabinoids or any of the excipients of the study medication; (h) Clinically relevant cardiac dysfunction within the last 12 months or had a cardiac disorder that, in the opinion of the investigator, would put the subject at risk of a clinically relevant arrhythmia or myocardial infarction; (i) Impaired renal function, i.e., serum creatinine clearance lower than 50 mL/min; (j) Significantly impaired hepatic function, at visit 1, in the investigator’s opinion and/or had liver function tests of equal to or greater than three times the upper limit of normal; (k) Pregnancy or breastfeeding; (l) Men with history of fertility problems and who plan to conceive at any time in the future; (m) Any participant who plans to conceive either at screening or while enrolled in the study; (n) Inability (or unwillingness) of women of childbearing potential and men to use a medically acceptable form of contraception throughout the study duration; (o) Any other significant disease or disorder which, in the opinion of the investigator, may either put the subject at risk because of participation in the study, may influence the result of the study, or the subject’s ability to participate in the study; (p) Intention to travel internationally, or to donate blood during the study.

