#### Secondary and exploratory outcomes

2.6.3

All the secondary – efficacy and safety – outcomes will be assessed at baseline, at week 4 and 12 weeks after the initial treatment period. Clinical efficacy outcomes are presented in Table 2. In addition, we will assess the success of participants’ blinding after the initial treatment period with the James Blinding Index (69). Blood tests will be conducted only at baseline and at week 4 to measure immunological and neurobiological markers. Safety measures will include all reported or observed adverse events and serious adverse events (AEs and SAEs). Pregnancy and birth control will be re-evaluated every 4 weeks.

**Table 2 tab2:** Secondary and exploratory efficacy assessments.

Test	Symptom	Type of outcome
Modified Ashworth Scale (42)	Spasticity, as assessed by a clinician	ClinRO
Expanded Disability Status Scale (43)	Disability	
Positive and Negative Syndrome Scale (45)	Psychotic symptoms	
Multiple Sclerosis Quality of Life Inventory (46, 47), including^a^:		PRO
MOS Pain Effects Scale (46, 47)	Pain	
Modified Fatigue Impact Scale – 5-Item Version (46, 47)	Fatigue	
Bowel Control Scale (46, 47)	Bowel dysfunction	
Bladder Control Scale (46, 47)	Bladder dysfunction	
Modified Social Support Survey – 5-Item Version (46, 47)	Perceived social support	
Sexual Satisfaction Scale (46–48)	Sexual dysfunction	
36-Item Short Form Survey (46, 47)	Quality of life	
Perceived Deficits Questionnaire (46, 47, 49)	Subjective cognitive function	
Pittsburgh Sleep Quality Index (50) and Epworth Sleepiness Scale (51)	Sleep issues, according to the assessment of sleep quality and sleepiness, respectively	
Restless Legs Syndrome Severity Rating Scale (52, 53)	Restless legs syndrome’s severity	
Hospital Anxiety and Depression Scale (54, 55)	Anxiety and depression	
Cannabis Experience Questionnaire (56, 57)^b^	Euphoric and paranoid-dysphoric effects of cannabis	
Battery of cognitive tests: Montreal Cognitive Assessment (58), Brief Visuospatial Memory Test–Revised (59), D-KEFS Color-Word Interference Test (60), Hopkins Verbal Learning Test–Revised (61), The Trial Making Test A/B (62), and Symbol Digit Modalities Test (63)	Objective cognitive function	PerfO
Timed 25 Foot-Walk test (64–66)	Mobility	

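### The age limit of 50 on the screening pregnancy test only removes older women who may still conceive, so they can start THC and/or CBD untested

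*Protocol article*

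**What the plan says.** Four parts of the protocol article bear on this.

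- **Screening (2.6.1)** sets out who is tested: "A pregnancy test and birth control questionnaire will be conducted in women aged ≤50 years with no sign of menopause". The sentence goes on to require that the woman has not had surgical contraception. All three conditions must be met.
- **Study population (2.3)** sets eligibility. The age criterion is "Aged 21 years or older", with no upper bound. Exclusion (k) reads "Pregnancy or breastfeeding", with no age qualifier. Exclusion (n) concerns the inability or unwillingness "of women of childbearing potential and men to use a medically acceptable form of contraception throughout the study duration". The article does not define childbearing potential.
- **Arms and intervention (2.5.1)** starts study treatment on day 1 and raises the daily amount "up to a maximum of 20 mg for THC and 200 mg for CBD, if well tolerated".
- **Secondary and exploratory outcomes (2.6.3)** adds one later check: "Pregnancy and birth control will be re-evaluated every 4 weeks". It does not say which participants are covered or whether the re-evaluation is a laboratory test.

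**The concern.** A targeted testing rule is reasonable: there is no purpose in testing women who cannot become pregnant. Here, though, the two usual reasons for exemption, menopause and surgical sterility, are already stated as conditions of their own. An age limit placed on top of them can exempt only women to whom neither reason applies. Those women are eligible by age and bound by the pregnancy exclusion.

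What is at stake is an early pregnancy that the woman does not know about. History-taking can establish whether she plans to conceive and what contraception she uses. It cannot reveal a pregnancy of which she is unaware. Without a test, she could be allocated to an arm containing THC, CBD or both, contrary to exclusion (k).

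**Working it through.** The core of this check is logical. The plan gives no figure to reproduce.

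**Step 1. Who is tested.** Let A be age 50 or under, M no sign of menopause, and S no surgical contraception. The rule in 2.6.1 tests a woman only if A, M and S all hold.

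**Step 2. What each condition removes.**

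- A, M and S all hold: tested.
- M or S fails, at any age: not tested. The reason is menopause or sterilisation, and A plays no part.
- M and S hold but A fails, that is, over 50, no sign of menopause, not sterilised: not tested, and age is the only reason.

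The third group is the whole effect of the age limit. Removing A changes nothing for anyone else.

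**Step 3. Whether that group can enter the trial.** The age criterion in 2.3 has a floor of 21 and no ceiling, so these women are eligible by age. Exclusion (k) applies to them because it has no age limit.

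**Step 4. Whether another pre-dose test covers them.** None is described.

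- Section 2.3 states that "All potential participants will be screened to determine their eligibility", and 2.6.1 has a neurologist evaluate eligibility, but neither adds a pregnancy test.
- The blood tests in 2.6.3, at baseline and week 4, are described as measuring immunological and neurobiological markers.
- The 4-weekly re-evaluation in 2.6.3 comes after the screening check and is not described as a condition for starting treatment.

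**Step 5. Exposure in one missed case.** Suppose the 4-weekly re-evaluation does include such a woman, does involve a test, and is counted from the first dose. The amount taken by then, at full titration, follows from Table 1:

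- THC in week 1: 4 + 4 + 8 + 8 + 16 + 16 + 20 = 76 mg.
- THC in weeks 2 to 4: 21 × 20 = 420 mg.
- THC over 28 days: 76 + 420 = 496 mg.
- CBD is ten times the THC amount throughout Table 1: 4,960 mg.

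That is the entire initial course. It describes one hypothetical participant and says nothing about how likely the event is. If the interval runs from screening, the amount is smaller; the article does not give the gap between screening and first dose.

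**Step 6. Number of women affected.** This cannot be derived. Section 2.3 gives the sex ratio of MS ("which is 2.6 higher in women than in men in Canada"), but the article gives no age distribution and no menopausal status. No count is offered here.

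**The case against.** The strongest reply has four parts.

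*The rule may itself be the trial's definition of childbearing potential.* The article does not define the term, a full protocol commonly would, and its absence from an article is no fault. This stands. A reader might infer that 2.6.1 contradicts exclusion (n), but the document does not establish that. If the full protocol ends childbearing potential at 50, the mismatch with (n) disappears.

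*Exclusion (k) has no limits at all, so any targeted rule is narrower than (k).* This is also correct, and it applies to the remedy proposed here, which would still exempt postmenopausal and sterilised women. Being narrower than (k) is therefore not a fault in itself. The difference is that menopause and sterilisation are reasons why a woman cannot conceive. The age limit takes effect only where both are absent.

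*Other safeguards apply at any age.* Criteria (k), (m) and (n), the medical history, the neurologist's evaluation and the investigator's discretion under (o) all cover women over 50, and nothing forbids a clinician from ordering a test. These safeguards reduce the risk. They do not replace a test for a pregnancy that is not yet recognised.

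*The event is improbable.* This is accepted, and it is why the point is rated minor.

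A reader might also infer that perimenopausal women of 50 or under go untested. That would require early signs to count as a sign of menopause, and nothing in the article supports that reading.

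**Conclusion.** The point holds, as a minor one. Read as written, 2.6.1 lets a woman over 50 who shows no sign of menopause and is not surgically sterile start study treatment without a pregnancy test, although she is eligible by age and subject to exclusion (k). The gap is in verification, not in eligibility: a woman known to be pregnant is still excluded at any age.

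The conclusion rests on the wording of the article alone and on the assumption that the full protocol adds no further pre-dose test. The affected group is probably small, and neither its size nor the number of pregnancies in it can be stated. No estimate, test or sample size is affected.

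**What to change.** In 2.6.1, delete the age condition, so that all women who are not postmenopausal and not surgically sterile have the pregnancy test and birth control questionnaire before the first dose. In 2.6.3, state that the 4-weekly re-evaluation covers the same women. If the full protocol defines childbearing potential, its definition should be brought into line with this wording.

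The cost is two short edits and a few more runs of procedures the trial already uses. If each re-evaluation includes a test, a newly covered woman has 2 tests (screening and week 4), or up to 5 if she is a responder followed to week 16 (screening and weeks 4, 8, 12 and 16). The downside is that small burden on women over 50 who are not menopausal. Randomisation, outcomes and analysis do not change. The article reports 41 participants randomised by May 29, 2024, against a target of up to 250, so at that date the change could still have applied to most of the planned sample.

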#### Primary outcome

2.6.2

The primary outcome (i.e., patient-reported spasticity) will be assessed using the mNRS (22, 44). The main outcome will be the difference in mNRS recorded for 7 days prior to the visit at week 4 and the visit at baseline. NRS is the most used tool to assess spasticity in most previous RCTs of treatment, including cannabinoid-based therapy, for MS-related spasticity (22). It is represented on a 0–10 scale, where 0 means no spasticity and 10, the worst possible spasticity (22). The NRS has been shown to be more robust than the Ashworth Scale for the test–retest reliability and highly correlative of the Patient Global Impression of Change scores (22, 44). Most studies investigating cannabis-derived products enrolled MS patients who have NRS ≥4 on the 0–10 scale (22). To include patients with moderate spasticity, we also enrolled those who have mNRS ≥2 on the 0–10 scale (17, 22, 44).

#### Secondary and exploratory outcomes

2.6.3

All the secondary – efficacy and safety – outcomes will be assessed at baseline, at week 4 and 12 weeks after the initial treatment period. Clinical efficacy outcomes are presented in Table 2. In addition, we will assess the success of participants’ blinding after the initial treatment period with the James Blinding Index (69). Blood tests will be conducted only at baseline and at week 4 to measure immunological and neurobiological markers. Safety measures will include all reported or observed adverse events and serious adverse events (AEs and SAEs). Pregnancy and birth control will be re-evaluated every 4 weeks.

**Table 2 tab2:** Secondary and exploratory efficacy assessments.

Test	Symptom	Type of outcome
Modified Ashworth Scale (42)	Spasticity, as assessed by a clinician	ClinRO
Expanded Disability Status Scale (43)	Disability	
Positive and Negative Syndrome Scale (45)	Psychotic symptoms	
Multiple Sclerosis Quality of Life Inventory (46, 47), including^a^:		PRO
MOS Pain Effects Scale (46, 47)	Pain	
Modified Fatigue Impact Scale – 5-Item Version (46, 47)	Fatigue	
Bowel Control Scale (46, 47)	Bowel dysfunction	
Bladder Control Scale (46, 47)	Bladder dysfunction	
Modified Social Support Survey – 5-Item Version (46, 47)	Perceived social support	
Sexual Satisfaction Scale (46–48)	Sexual dysfunction	
36-Item Short Form Survey (46, 47)	Quality of life	
Perceived Deficits Questionnaire (46, 47, 49)	Subjective cognitive function	
Pittsburgh Sleep Quality Index (50) and Epworth Sleepiness Scale (51)	Sleep issues, according to the assessment of sleep quality and sleepiness, respectively	
Restless Legs Syndrome Severity Rating Scale (52, 53)	Restless legs syndrome’s severity	
Hospital Anxiety and Depression Scale (54, 55)	Anxiety and depression	
Cannabis Experience Questionnaire (56, 57)^b^	Euphoric and paranoid-dysphoric effects of cannabis	
Battery of cognitive tests: Montreal Cognitive Assessment (58), Brief Visuospatial Memory Test–Revised (59), D-KEFS Color-Word Interference Test (60), Hopkins Verbal Learning Test–Revised (61), The Trial Making Test A/B (62), and Symbol Digit Modalities Test (63)	Objective cognitive function	PerfO
Timed 25 Foot-Walk test (64–66)	Mobility	

ClinRO, clinician-reported outcome; PRO, patient-reported outcome; PerfO, performance outcome. ^a^We adapted the Multiple Sclerosis Quality of Life Inventory for the CANSEP trial, by excluding two of its ten scales: (1) The Impact of Visual Impairment Scale was not included, because it is not widely used in clinical practice and not relevant to the CANSEP trial; (2) instead of the Mental Health Inventory, we considered the Hospital Anxiety and Depression Scale, a widely used instrument in clinical practice, but also a validated scale in the MS population (55, 67, 68). Furthermore, we added the Cannabis Experience Questionnaire for the subjective effects of cannabinoids (56, 57). ^b^All tests will be conducted at baseline, at week 4, and at week 16. However, participants who never used cannabis in their lifetime will not complete the Cannabis Experience Questionnaire at baseline.

### Data analyses

2.7

The data will be analyzed once all randomized subjects have completed the trial. Analyses of primary and secondary outcomes will rely on the intention-to-treat paradigm. Thus, all initially randomized subjects will be included. Descriptive statistics will be used to compare the baseline characteristics of subjects. They will include means, medians, standard deviations and interquartile ranges for continuous variables, and frequencies and percentages for categorical variables. Sensitivity analysis will be performed to the first few participants who did not complete the NRS scale as per the last version of the protocol and consequently have a different primary outcome measure.

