### Study design

2.2

CANSEP is a double-blinded, randomized, factorial, placebo-controlled trial in a cohort of PwMS with an incomplete response to standard treatments, using various measurements, and thorough, multidisciplinary outcomes. Up to 4 visits are scheduled during this trial. Visit 1 is dedicated to the consent process and the confirmation of eligibility criteria. Outcomes assessments are done during visit 2 (baseline) and during visit 3 which takes place after 4 weeks of treatment. Finally, outcomes assessments are also carried out during a fourth visit which is scheduled 12 weeks after the end of the initial treatment period for responders only, i.e., patients who have a decrease in mean Numeric Rating Scale (NRS) of at least one point compared to baseline. Indeed, spasticity will be assessed using the NRS (22), but the spasticity outcome analyzed in this trial will be the mean NRS score over 7 days (mNRS). Blood samples will be collected to measure immunological and neurobiological markers in order to investigate the underlying physiological responses of each treatment administration, and to identify potential mechanisms of their therapeutic effects. The study plan is represented in Figure 1.

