#### Secondary and exploratory endpoints

2.7.3

The secondary and exploratory outcomes will be analyzed using the same methods as spasticity. Exploratory outcomes and mechanistic factors (sex, neurobiological markers, age, etc.) will be analyzed using ANCOVA models.

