##### Safety analyses

2.7.3.2

AEs will be analyzed using the Common Terminology Criteria for Adverse Events (version 5.0) according to the Medical Dictionary for regulatory activities (79). The frequency and percentage of participants experiencing each specific AE will be tabulated by severity and treatment. Each AE will be counted once under the maximum severity or the strongest recorded causal relationship to the studied product. For each arm, all AEs will be grouped by organ class and, for each AE, the relative risk and absolute risks between arms with their 95% confidence intervals will be calculated.

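### Only week-4 responders reach week 16, so the all-randomized rule for secondary outcomes cannot hold there, and adverse-event risks without a time window compare arms over unequal exposure

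*Protocol article*

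**What the plan says.** **Who is observed to week 16.** Study design (2.2) sets "a fourth visit which is scheduled 12 weeks after the end of the initial treatment period for responders only", and defines responders as "patients who have a decrease in mean Numeric Rating Scale (NRS) of at least one point compared to baseline". Arms and intervention (2.5.1) gives the matching exposure: "Participants will receive the allocated treatment for a total of 4 consecutive weeks, followed by an additional 12 weeks of treatment for responders".

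**What is measured then.** Secondary and exploratory outcomes (2.6.3) says that secondary efficacy and safety "outcomes will be assessed at baseline, at week 4 and 12 weeks after the initial treatment period". The note to Table 2 adds "All tests will be conducted at baseline, at week 4, and at week 16". Neither sentence mentions the restriction to responders.

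**How it is analysed.** Data analyses (2.7) states "Analyses of primary and secondary outcomes will rely on the intention-to-treat paradigm. Thus, all initially randomized subjects will be included". Section 2.7.3 states "The secondary and exploratory outcomes will be analyzed using the same methods as spasticity". Those methods, in Primary endpoints (2.7.2), are ANOVA on the change from baseline to week 4 and ANCOVA on the post-intervention score. The baseline-value imputation in Missing data and dropouts (2.7.5) covers the primary outcome only.

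**Safety.** Section 2.6.3 collects every reported or observed adverse event. Safety analyses (2.7.3.2) counts each event once, at its maximum severity or strongest causal link, and then says "for each AE, the relative risk and absolute risks between arms with their 95% confidence intervals will be calculated". It gives no time window, split by phase or person-time rate.

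**The concern.** Response is measured after randomization, and the trial's hypothesis (1.1) is that the active treatments increase it. Two consequences follow.

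1. *Efficacy at week 16.* Non-responders have no visit 4, so an analysis of all randomized participants is impossible there. Comparing those who do attend is not a randomized comparison: the placebo participants present are those who improved without active drug, and the active participants present are a broader group.
2. *Adverse events.* An arm with more responders is treated and observed for longer. Counting each event once over whatever time a participant was observed gives that arm more opportunity to record one. An effective treatment would then look less safe than it is. Tolerability is the second main aim (1.2), so this bears on a principal result.

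**Working it through.** **Inputs from the documents.** Response threshold: a fall of 1 point. Exposure: 4 weeks for non-responders, 16 for responders. Mean change treated as the minimal clinically significant effect: −1.55; the larger effect considered: −1.90 (both in 2.7.1). The article gives no SD, placebo change, responder rate, event rate or week-16 figure, so there is no plan figure to reproduce on this point. Everything below is illustrative.

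**Assumed.** Normal change scores with SD 1.5 to 2.5; placebo mean −0.5 or −1.0; active mean −1.55 or −1.90; correlation ρ between week-4 and week-16 change of 0.5 or 0.7; no true change in the arm difference between the two visits.

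**Step 1: responder proportion.** P(response) = Φ(c), with c = (−1 − mean)/SD. For SD 1.5:
- placebo (mean −0.5): c = −0.333, so 37% respond
- active (mean −1.55): c = 0.367, so 64% respond

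Over the whole grid, 37–50% respond on placebo and 59–73% on active.

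**Step 2: adverse events, the direct problem.** With equal weekly hazard h in both arms and responder proportion r, the crude risk is

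R(r) = (1 − r)(1 − e^(−4h)) + r(1 − e^(−16h)).

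For h = 0.02, the 4-week risk is 0.077 and the 16-week risk 0.274.
- Placebo, r = 0.37: 0.63 × 0.077 + 0.37 × 0.274 = 0.150
- Active, r = 0.64: 0.36 × 0.077 + 0.64 × 0.274 = 0.203
- Relative risk 0.203/0.150 = 1.36; absolute difference about 5 percentage points; true effect none.

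Mean exposure is 4 + 12 × 0.37 = 8.4 weeks against 4 + 12 × 0.64 = 11.7 weeks, a ratio of 1.38. Varying h from 0.005 to 0.10:

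| Responders, placebo vs active | Crude relative risk | Weeks 0–4 only |
|---|---|---|
| 37% vs 64% | 1.25–1.38 | 1.00 |
| 50% vs 60% | 1.08–1.12 | 1.00 |
| 50% vs 50% | 1.00 | 1.00 |

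If events cluster early, the excess shrinks. With the extension hazard set to one quarter of the initial hazard and h = 0.02, the first row falls from 1.36 to 1.15.

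**Step 3: week-16 spasticity among responders, if arms were compared.** The expected week-16 change among responders is mean − ρ × SD × φ(c)/Φ(c). With SD 1.5 and ρ = 0.5:
- placebo: −0.5 − 0.75 × 1.021 = −1.27
- active: −1.55 − 0.75 × 0.580 = −1.99
- observed difference −0.72, against a true −1.05 (68% retained).

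With ρ = 0.7 it is −0.59 (56%). Over the grid, about 56% to 72% of the true difference is retained.

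**Step 4: other secondary outcomes.** Here the shift depends on the correlation with week-4 spasticity change. At a correlation of 0.3 in the same scenario it is 0.3 × (1.021 − 0.580) = 0.13 SD. At SD 1.4 with means −1.0 and −1.55 it is 0.3 × (0.798 − 0.566) = 0.07 SD. If the outcome has no true effect, that shift is a spurious difference rather than an attenuation. If it is uncorrelated with spasticity change, there is no shift.

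**The case against.** The strongest reply is that no sentence orders a between-arm test at week 16. Sections 2.6.3 and the Table 2 note say when outcomes are assessed, not what is compared. Section 2.7.3 borrows the primary's methods, and 2.7.2 ties those to week 4. Read together, these could describe a coherent week-4 analysis of everyone randomized. This stands. A reader might infer that the plan prescribes a biased week-16 comparison; the text does not go that far. What it does do is schedule secondary outcomes at week 16, put secondary analyses under an all-randomized rule, and never limit that rule to week 4.

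On safety, the reply is that a phase split or person-time rate is ordinary detail for a full analysis plan. That is partly fair: the article does not say that the phases are pooled. But it does fix the measure (each event counted once, crude relative and absolute risks between arms) on all reported events. Followed as written, that measure mixes 4 and 16 weeks of exposure.

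The size is also open to challenge. A reader might take the week-4 change among responders as the week-16 result, which shrinks a 0.55-point difference to 0.23 (SD 1.4, means −1.55 and −1.0). That holds only if the week-4 and week-16 changes are perfectly correlated; the same inputs give 0.32 at correlation 0.7 and 0.39 at 0.5. The adverse-event figures assume a constant hazard, whereas doses are raised during week 1 and events may cluster there.

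**Conclusion.** The point holds in a limited form. The all-randomized rule cannot be met at week 16, and the article does not say that secondary between-arm comparisons stop at week 4. The adverse-event rule, applied as written, gives a false excess to whichever arm has more responders. That excess is a relative risk of about 1.1 to 1.4, given assumed placebo and active responder rates between 37% vs 64% and 50% vs 60%, and a constant equal hazard. It is lower with early clustering, higher if responder rates differ more, and zero if they are equal.

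A reader might conclude that the trial's efficacy results are biased. They are not: the primary outcome and every week-4 comparison are untouched. Nor does selection always pull week-16 differences toward zero. For secondary outcomes its size and direction depend on their correlation with spasticity change, about which the documents give nothing.

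**What to change.** - In 2.7 and 2.7.3, state that between-arm comparisons of secondary efficacy outcomes are made at week 4 in all randomized participants. State that week-16 results are reported within arm, among responders, as descriptive and non-randomized.
- In 2.7.3.2, compute between-arm relative and absolute adverse-event risks for weeks 0 to 4 in all randomized participants. Tabulate extension-phase events separately by arm, with person-time rates.

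The cost is a few sentences and one extra table. The trial gives up any inferential between-arm claim at week 16. No visit, measurement or sample size changes, and because analysis waits until all randomized participants have finished, the wording can be settled before the data are unblinded for analysis.
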